## Abstract

**Background:**

Effective follow-up care plays a critical role in enhancing breast cancer outcomes, as diagnosing breast cancer in earlier stages can improve mortality and ease treatment burden. Individuals with unmet social needs face greater barriers in completing their follow-up care (e.g., additional imaging, biopsies, and surgery). They are two times less likely to complete follow-up appointments. When patients do not complete follow-up appointments, they are at higher risk of detecting breast cancer at a later stage. We aim to examine how a social needs intervention via community navigation may (1) address patients’ social needs, and (2) improve the completion of recommended medical care following an abnormal mammography.

**Methods:**

This is a single-center randomized controlled trial taking place in the Intermountain West. We plan to enroll 1,450 participants throughout the study. Women with abnormal mammography results will be invited to complete a validated, 10-item social needs screening assessment in English or Spanish. Eligible patients will be at least 18 years of age, speak English or Spanish, and indicate at least one social need. Participants will be randomized to passive or active social needs categories. Those in the active group will be called by 211 United Way services (211), a service which connects callers to community resources. The passive group will not receive a call from 211. Instead, they will be provided with information to contact 211 independently if they choose to. Primary outcomes are: (1) change in social needs, and (2) follow-up of abnormal mammography results, and will be assessed through follow-up surveys and chart reviews. Interviews and focus group discussions will explore how social needs influence patients’ adherence to recommended follow-up after an abnormal mammography result, and the role of community service navigation assistance in that follow-up.

**Discussion:**

This study utilizes a 10-item social needs assessment and community navigation services to address social needs that prevent women from receiving timely follow-up after an abnormal mammogram screening. Our goal is to improve breast cancer follow-up outcomes for women with social needs.

**Trial registration:**

The study was pre-registered at ClinicalTrials.gov on March 12, 2024, under identifier NCT06305312.

## Background

An estimated 42,680 people in the U.S. will die from breast cancer in 2025 [1]. Access to mammogram services, follow-up care, and early detection are associated with higher survival rates [2–6]. After an abnormal mammogram result, recommended follow-up care may include additional diagnostic imaging, a biopsy, or a visit with a healthcare provider. Receiving this follow-up care is crucial for improved breast cancer outcomes, as diagnosing breast cancer in earlier stages can improve mortality and also ease treatment burden [7]. Individuals with social needs face greater barriers in completing their follow-up care (e.g., additional imaging, biopsies, and surgery [8]) and are half as likely to complete follow-up appointments [9].

Barriers to healthcare access can include insufficient housing, lack of transportation, prohibitive cost of healthcare visits, lack of social support, and need for childcare [10]. These factors, if unmet, are known as “social needs” [11]. The need to implement programs to ease the burden of social needs or improve access to resources is well documented [12]. While the impact of social needs on health outcomes is widely recognized, further work is needed to improve access to social needs resources and to increase patients’ ability to attend follow-up appointments [13]. 

Prior research has shown successful implementation of a 10-item social needs assessment called SINCERE, as well as outreach from a community service navigator in an emergency department setting [14–16]. SINCERE stands for Screener for Intensifying Community Referrals for Health. The 10 questions chosen for this measure are centered around social needs, that if unmet, make it difficult for patients to complete healthcare visits. To expand on this, the present research aims to apply social needs screening using the SINCERE assessment, and community support services for those who receive abnormal mammography results and need to complete subsequent episodes of care. In the context of this study, “episode completion” means that the patient completes the next steps in care after receiving an abnormal mammogram result as suggested by their medical team. These episodes can mean completing additional imaging, receiving a biopsy, or attending another clinic visit. We will compare participants who receive the 211 social services navigation vs. participants who are only given the phone number for 211 social services. Ultimately, we aim to improve breast cancer screening episode completion and early detection of breast cancer.

### Hypotheses and aims

Central hypothesis: Community services navigation combined with social needs referrals will increase use of social services and improve breast cancer screening follow-up compared to the passive process of social service referrals alone.

Aim 1: Test whether the use of a community services navigation intervention in conjunction with social service referrals decreases social needs compared to the referrals alone (usual care).

Aim 1 Hypothesis: Patients who receive community services navigation will have fewer social needs over time when compared to patients who receive standard of care process of social service referrals alone.

Aim 2: Determine the impact of the community services navigation intervention (211 services) on breast cancer screening episode completion and preventive care utilization among women with self-reported social needs.

Aim 2 Hypothesis: Patients who receive the community services navigation intervention will complete their breast screening episode of care, e.g. additional imaging, follow-up visits, or biopsy and recommended follow-up and preventative services more than women who do not.

Aim 3: Qualitatively examine multilevel facilitators and barriers to successful engagement with community services and episode completion among underserved women with an abnormal breast cancer screen and self-reported social needs and explore the role of community service navigation.

## Methods and design

### Study design

We will conduct a randomized controlled trial (RCT) within a mixed-methods sequential explanatory study [17]. We will use a single-center RCT to assess how community services navigation from United Way 211 Community Services (hereafter referred to as 211), impacts social needs and breast cancer screening episode completion. This will be followed by a qualitative phase designed to help explain the quantitative results obtained in the RCT. We will recruit 1,450 patients from multiple mammography clinics within the University of Utah health system, including mobile buses that serve rural Utah populations. The study protocol was reviewed and approved by the University of Utah IRB and is registered at clinicaltrials.gov NCT06305312. Figure 1 shows the study flow.

**Fig. 1 Fig1:**
[figure not shown]
B-Sincere study schema

This clinical trial protocol follows the SPIRIT guidelines [18].

## Procedures

### Phase 1 – RCT

#### Recruitment and participation criteria

Eligible patients are those who are 18 and older, have completed a routine mammogram screening appointment and received an abnormal result (BI-RADS scores, e.g., scores 0, 3, 4, and 5), speak English or Spanish, and do not currently have a diagnosis of breast cancer. Individuals who have had a mammogram with an abnormal result will be recruited via study coordinator efforts as soon as their result is available in the medical record (usually within a few days of the exam). Participants will be invited to participate through multiple means (email, text, phone calls). Interested individuals will be asked to complete the 10-item SINCERE assessment to determine eligibility for the study. If patients indicate at least one social need on the SINCERE assessment, they will be invited to join the study. If they have no social needs, they are not deemed eligible for participation. Participants who indicate having a social need but decide they do not want to participate will be given 211’s contact information should they want to reach out independently. Any participant who requests to be withdrawn from the study can end their participation at any time by requesting to be withdrawn by contacting study staff.

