#### Intervention

After providing informed consent and authorization, all participants will be randomized using the REDCap randomization function, with equal allocation to two arms: the usual care group or the active referral group.

The usual care group is provided the contact information for 211 if they choose to use it, but 211 does not reach out to these participants. 211 will receive the information of all participants, including those in the usual care group. If a usual care group participant reaches out to 211, they will note this for study records.

211 will reach out to all patients randomized to the active referral group within 48 h of receiving their information via REDCap. The 211 team will discuss the reported social needs with participants and match them with appropriate community resources that can help address their social needs. The 211 teams will also follow up again at 2 weeks with participants to ask if the participant has connected with services and offer additional support connecting to the social service referrals as needed.

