#### Outcomes

The primary outcomes for this study are (1) change in participants’ social needs, and (2) episode completion. Social needs are determined by the SINCERE assessment, which the participant takes at baseline, 1 month, 6 months, and 18 months [15]. Episode completion in regard to follow-up care will be determined by patient-reported surveys and by accessing the patient’s electronic health record (EHR) to determine if they attended their follow-up care appointment(s) (e.g. additional imaging, biopsy, meeting with a specialist, or starting breast cancer treatment). As in our prior work within the national PROSPR I consortium ([name], MPI) [20], we define a breast screening episode follow-up within a specified time interval based on Breast Imaging-Reporting and Data System (BI-RADS) category [21, 22]; specifically: BI-RADS 0,4,5 – episode completion within 3 months; BI-RADS 3 – episode completion within 9 months. The BI-RADS 3 classification is used infrequently (~ 2% of patients nationally, and < 1% at the University of Utah), and therefore, we anticipate we will capture > 99% of follow-up at our 6-month data collection point [21]. Data on both episode completion and time to completion will be collected.

The secondary outcomes are (1) social service utilization and (2) prevention and screening behaviors relating to breast, cervical, colorectal, and colon cancers. Health outcomes include trust in the healthcare system [25], cancer worry [26], and social support [27]. These will be assessed through patient reported outcomes at various timepoints throughout study enrollment.

Social service utilization data is gathered through patient reported measures as well as reports from 211 on participant utilization of social services. 211 records outcome at follow up, referral outcome, and if the patient’s situation has changed. Prevention and screening behaviors include next annual mammogram, cervical cancer screening, and colorectal cancer screening. We will ask women to self-report, and will also examine EHR records to capture guideline-concordant use of wellness visits.

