#### Analysis

For the primary outcomes of change in participant level of social need and episode completion, we will use mixed effects modeling, assuming missing at random, to determine if patients who receive community services navigation have greater reduction in social needs and if patients who receive the intervention complete their breast cancer screening episode of care and recommended follow up care. We will examine the interaction between time (conditional on baseline, 6, and 18 months) and intervention. We will analyze the time to follow-up completion using Cox proportional hazard modeling.

For the secondary outcome of community resource use, we will use a similar mixed-effects two-level model and utilize a log link function for a negative binomial regression for the count of social services used. We assume that the number of services will not be normally or dichotomously distributed. For the other secondary outcome of screening behavior, we will use the same mixed-effects two level model with log link function for a negative binomial regression.

Participant demographics will be compared between groups via t-Test and Fisher exact testing, Chi-squared testing, or Wilcoxon-Mann-Whitney test where appropriate.

To determine the sample size, power and sensitivity analyses were conducted with G-Power 3.1. We used a RMANOVA model with 3 total measures as a conservative approach for our mixed-effects model. We assume power = 0.95, alpha = 0.05, and two-tailed significance testing. Results indicate a small effect size (Cohen’s d = 0.09) can be detected. Therefore, recruitment of 1,450 patients with an attrition rate of 20%, will result in an analyzed sample of 1,160, which is sufficient power to detect a clinically meaningful effect. Unpublished pilot data obtained from participants who reported they had a social need the average amount of social needs was 3.06 with a standard deviation = 2.08. We will have 95% power to detect a reduction of social needs to 2.87.

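### Eligibility does not require follow-up to be still outstanding at randomisation, so women whose episode is already complete can enter and dilute the Aim 2 comparison

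*Protocol article*

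**What the plan says.** All references are to the protocol article.

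- **Recruitment and participation criteria.** Women must be adults (18 or over) who "have completed a routine mammogram screening appointment and received an abnormal result (BI-RADS scores, e.g., scores 0, 3, 4, and 5), speak English or Spanish". Only one criterion concerns disease status, namely that they "do not currently have a diagnosis of breast cancer". They must also report at least one need on the SINCERE screen. Coordinators begin recruiting "as soon as their result is available in the medical record (usually within a few days of the exam"). The approach is by several routes: "Participants will be invited to participate through multiple means (email, text, phone calls").
- **Intervention.** After consent, "all participants will be randomized using the REDCap randomization function, with equal allocation to two arms". The active contact follows: "211 will reach out to all patients randomized to the active referral group within 48 h of receiving their information via REDCap".
- **Outcomes.** Episode completion is the second primary outcome, with windows by category: "BI-RADS 0,4,5 – episode completion within 3 months; BI-RADS 3 – episode completion within 9 months". The start of these windows is not given. Imaging, biopsy, a specialist meeting and the start of treatment are listed as examples of follow-up care.
- **Analysis.** "We will analyze the time to follow-up completion using Cox proportional hazard modeling". No time origin is given.

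**The concern.** Recruitment and the clinic's own recall both start from the same abnormal result. Before a woman can be randomised she must be reached, return the SINCERE screen and consent, and the 211 call comes after that. Nothing in the criteria stops her from finishing her work-up in the meantime. The one exclusion based on her status, a current breast cancer diagnosis, removes those whose work-up found cancer. It does not remove those whose work-up was benign or negative.

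For such a woman the completion outcome is settled before allocation. She counts as a success in whichever arm she joins. Each one adds the same certain success to both sides, raises the apparent completion rate under usual care and pulls the contrast toward zero. The stake is a primary outcome: navigation that helps women with an open episode could be read as ineffective.

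**Working it through.** **The plan's own figure.** The Analysis section gives 1,450 enrolled, 20% attrition and 1,160 analysed (1,160 / 0.80 = 1,450, which agrees). Its 95% power is for social needs. Treated as a group-by-time interaction with three measures and an assumed correlation of 0.5, it reproduces at about 94%. No completion rate, effect or power is given for episode completion, so the figures below rest on assumed rates.

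**Dilution.** Let q0 and q1 be completion in the usual-care and active arms among women still outstanding, and f the share already complete at randomisation, equal across arms by randomisation.

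- Observed rate in each arm: p = f + (1 - f)q.
- Observed difference: p1 - p0 = (1 - f)(q1 - q0).
- Power, two-sided 5%: Φ(Δ/SE - 1.96), with SE = √{[p0(1 - p0) + p1(1 - p1)]/n}.

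**Inputs.** q0 = 0.65 and q1 = 0.73 (assumed); n = 1,450/2 = 725 per arm (equal allocation, no attrition).

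**Worked case, f = 20%.**

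- All women kept: p0 = 0.20 + 0.80 × 0.65 = 0.720 and p1 = 0.20 + 0.80 × 0.73 = 0.784, so Δ = 0.064. SE = √[(0.2016 + 0.1693)/725] = 0.0226. Power = Φ(2.83 - 1.96) = 81%.
- Already-complete women left out, no replacement: n = 725 × 0.80 = 580 and Δ = 0.08. SE = √[(0.2275 + 0.1971)/580] = 0.0271. Power = Φ(2.96 - 1.96) = 84%.

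| f | Observed difference (points) | Power, all kept | Power, left out without replacement |
|---|---|---|---|
| 0 | 8.0 | 91% | 91% |
| 10% | 7.2 | 87% | 88% |
| 20% | 6.4 | 81% | 84% |
| 30% | 5.6 | 74% | 79% |

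**Other assumed rates.** With 60% versus 70% and 580 per arm (1,160 analysed), power with all women kept is 95%, 91%, 86% and 79% at f = 0, 10, 20 and 30%. The pattern is the same.

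**How f depends on delay.** Assume a constant completion rate with a median of 30 days from the result. The share complete by day R is then 1 - 2^(-R/30): 11% at day 5, 28% at day 14 and 48% at day 28.

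**Cox model.** A large-sample simulation used those assumptions, a true hazard ratio of 1.25 after randomisation, time counted from the result and censoring at 90 days. It estimated 1.21, 1.16 and 1.11 for randomisation at day 5, 14 and 28. Across medians of 20 to 45 days, f ran from 7% to 62% and the estimate from 1.22 down to 1.08. Restricting to women still outstanding, with time from randomisation, returned 1.24 to 1.25 throughout.

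**The case against.** The strongest reply is that the problem may be small. Coordinators act within days of the exam. If most women are randomised near day 5, the simulated hazard ratio is still 1.20 to 1.22 against a true 1.25, and at f = 10% leaving the completed women out gains only about one point of power. The Background also describes the intervention as meant for women who still have next steps to complete, and an open-episode rule may stand in the full protocol. This stands as a limit on size. It does not close the gap: prompt recruitment fixes the first approach and not the date of consent, and the criteria as stated admit late responders.

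Three stronger readings are tempting, and the documents do not support them.

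- *Pre-randomisation events are put into the Cox analysis.* No time origin or risk set is stated, and the full protocol or analysis plan may set them. This is a risk, not a stated fact.
- *Any woman who has had her extra imaging is already complete.* The Background defines completion by the next steps that the medical team suggests, and these may go on to biopsy or a specialist visit. One visit completes some episodes and not others.
- *The result is biased toward one arm.* Randomisation balances early completers, so the effect is dilution and lost power.

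**Conclusion.** The point holds in a limited form. The stated criteria allow randomisation of women whose episode is already complete, and each such woman is uninformative for Aim 2. The shrinkage by (1 - f) is exact if f is equal across arms. The size of the loss is not known, because the documents give neither f nor completion rates. Under 65% versus 73% with 725 per arm, the cost is about 4, 10 and 17 points of power at f = 10, 20 and 30%. It is minor if randomisation follows the result within days and material if it commonly takes weeks. The Cox model carries the same exposure only if its time origin precedes randomisation. The sponsor should settle this before the Aim 2 data are analysed.

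**What to change.** 1. Keep all randomised women in the Aim 1 analysis.
2. Define the primary Aim 2 analysis set as women whose recommended follow-up of the index mammogram was not complete at randomisation. Judge this from health-record events dated before randomisation, with the same rule in both arms. Status fixed before allocation does not depend on arm, so the randomised comparison is preserved.
3. Start time to completion at randomisation in the Cox model.
4. Report the all-randomised Aim 2 analysis as a sensitivity analysis, and report f.
5. Optionally, for future enrolment, add an open-episode criterion checked in the health record on the day of randomisation.

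**Cost.** Items 1 to 4 need only record data that the trial already plans to extract. The Aim 2 set shrinks by f, yet power is higher than with everyone kept at each f above zero shown. Follow-up done outside the health system may be missed, but equally in both arms. Item 5 costs more: it turns away women who are valid for Aim 1, and holding 1,450 requires 1,450/(1 - f) otherwise eligible, consenting women. That is about 1,611 at f = 10% and 2,071 at f = 30%, so recruitment slows in proportion to f.

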#### Intervention

After providing informed consent and authorization, all participants will be randomized using the REDCap randomization function, with equal allocation to two arms: the usual care group or the active referral group.

The usual care group is provided the contact information for 211 if they choose to use it, but 211 does not reach out to these participants. 211 will receive the information of all participants, including those in the usual care group. If a usual care group participant reaches out to 211, they will note this for study records.

211 will reach out to all patients randomized to the active referral group within 48 h of receiving their information via REDCap. The 211 team will discuss the reported social needs with participants and match them with appropriate community resources that can help address their social needs. The 211 teams will also follow up again at 2 weeks with participants to ask if the participant has connected with services and offer additional support connecting to the social service referrals as needed.

#### Data collection

Data will be gathered through patient-reported outcome measures and extracting data from the patient’s health record. Participants will be asked to complete surveys at baseline, 6, 12, and 18 months after baseline. Surveys will be distributed through a REDCap survey link sent to participants at the appropriate time point via text or email. The Dillman total design principles for survey follow-up will be used in our survey approach [19].

#### Outcomes

The primary outcomes for this study are (1) change in participants’ social needs, and (2) episode completion. Social needs are determined by the SINCERE assessment, which the participant takes at baseline, 1 month, 6 months, and 18 months [15]. Episode completion in regard to follow-up care will be determined by patient-reported surveys and by accessing the patient’s electronic health record (EHR) to determine if they attended their follow-up care appointment(s) (e.g. additional imaging, biopsy, meeting with a specialist, or starting breast cancer treatment). As in our prior work within the national PROSPR I consortium ([name], MPI) [20], we define a breast screening episode follow-up within a specified time interval based on Breast Imaging-Reporting and Data System (BI-RADS) category [21, 22]; specifically: BI-RADS 0,4,5 – episode completion within 3 months; BI-RADS 3 – episode completion within 9 months. The BI-RADS 3 classification is used infrequently (~ 2% of patients nationally, and < 1% at the University of Utah), and therefore, we anticipate we will capture > 99% of follow-up at our 6-month data collection point [21]. Data on both episode completion and time to completion will be collected.

The secondary outcomes are (1) social service utilization and (2) prevention and screening behaviors relating to breast, cervical, colorectal, and colon cancers. Health outcomes include trust in the healthcare system [25], cancer worry [26], and social support [27]. These will be assessed through patient reported outcomes at various timepoints throughout study enrollment.

Social service utilization data is gathered through patient reported measures as well as reports from 211 on participant utilization of social services. 211 records outcome at follow up, referral outcome, and if the patient’s situation has changed. Prevention and screening behaviors include next annual mammogram, cervical cancer screening, and colorectal cancer screening. We will ask women to self-report, and will also examine EHR records to capture guideline-concordant use of wellness visits.

Individual characteristics are derived both from the EHR and patient reported outcomes. Individual characteristics reported from the EHR include the Charlson Comorbidity Index [28], need factors (breast cancer risk, estimated with the Tyrer-Cuzick risk model [29]), environmental characteristics such as rural vs. urban residence based on ZIP code (categorized in the 4-tier Rural Urban Commuting Area (RUCA) schema) [30], area deprivation index (ADI) or patients’ census tract of residence per geocoded EHR-based address [31]. Individual characteristics reported by the patient include reported availability of services, predisposing factors (age, language, race and ethnicity, health literacy [32–34]), enabling factors including health care access, global health [23], and depression [24].

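### Social service utilization draws on 211 reports that are actively collected only in the active arm; if they enter the between-arm count, the comparison can favour the intervention when true use is equal

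*Protocol article*

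**What the plan says.** The Outcomes section makes this the first secondary outcome ("The secondary outcomes are (1) social service utilization") and names two sources for it: "Social service utilization data is gathered through patient reported measures as well as reports from 211 on participant utilization of social services". It adds that "211 records outcome at follow up, referral outcome", together with whether the woman's situation has changed.

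The Intervention section makes contact with 211 depend on the arm:

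- **Active referral:** "211 will reach out to all patients randomized to the active referral group", within 48 hours of receiving their details. Then: "The 211 teams will also follow up again at 2 weeks with participants to ask if the participant has connected with services".
- **Usual care:** women receive the 211 contact details, "but 211 does not reach out to these participants". "If a usual care group participant reaches out to 211, they will note this for study records".

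The Analysis section plans a mixed-effects negative binomial regression on the number of social services used. It does not name the source of that number or a rule for combining the two sources.

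**The concern.** Everything 211 is said to record needs a contact with 211. That contact is scheduled for every woman in one arm and left to the woman's own initiative in the other. A usual-care woman who finds help without phoning 211 can be counted only if she reports it in a survey. An active-arm woman with the same use can be counted through the survey or through 211. If both sources feed the count, the active arm is measured with a more sensitive instrument.

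The second source is also not blinded. 211 holds the details of all participants but calls only one arm, so it knows the allocation, and it delivers the intervention.

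The stake is the first half of the central hypothesis, that navigation "will increase use of social services and improve breast cancer screening follow-up". Use of services is the step through which navigation is meant to reduce needs and help women complete follow-up. An inflated utilization result would lend false support to that mechanism.

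**Working it through.** The article gives no rate, effect size or power for service utilization, so there is no figure for this outcome to reproduce. The one stated figure used here is the analysed sample: 1,450 × (1 − 0.20) = 1,160, as the Analysis section says. With equal allocation this is 580 per arm.

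**Inputs from the article:** 580 per arm; two-sided 0.05 (stated for the sample size calculation and borrowed here); a negative binomial model for a count.

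**Inputs assumed (none is in the article):**

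- true mean of 1 service per woman in both arms, so no true effect
- negative binomial dispersion of 1
- s = share of services captured by the survey, the same in both arms
- c = share of the services missed by the survey that 211 picks up when it is in contact with the woman
- q = share of usual-care women who phone 211

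**Formulas, if the count takes a service recorded by either source:**

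- observed mean, active: m1 = s + (1 − s)c
- observed mean, usual care: m0 = s + (1 − s)cq
- spurious rate ratio: RR = m1/m0
- SE of log RR = √[(1/m1 + 1)/580 + (1/m0 + 1)/580]
- z = log RR / SE; false-positive rate = Φ(z − 1.96) + Φ(−z − 1.96)

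This uses one count per woman and a Wald test, which is simpler than the planned two-level model.

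| s | c | q | m1 | m0 | RR | SE | z | False-positive rate |
|---|---|---|---|---|---|---|---|---|
| 0.9 | 0.1 | 0.1 | 0.910 | 0.901 | 1.01 | 0.085 | 0.12 | 5.2% |
| 0.8 | 0.1 | 0.1 | 0.820 | 0.802 | 1.02 | 0.088 | 0.25 | 5.7% |
| 0.7 | 0.1 | 0.1 | 0.730 | 0.703 | 1.04 | 0.091 | 0.41 | 7.0% |
| 0.8 | 0.3 | 0.2 | 0.860 | 0.812 | 1.06 | 0.087 | 0.66 | 10% |
| 0.6 | 0.5 | 0.1 | 0.800 | 0.620 | 1.29 | 0.092 | 2.78 | 80% |

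The last row in full: m1 = 0.6 + 0.4 × 0.5 = 0.80; m0 = 0.6 + 0.4 × 0.5 × 0.1 = 0.62; RR = 0.80/0.62 = 1.29.

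The direction does not depend on the inputs: RR exceeds 1 whenever the survey misses some use (s < 1), 211 finds some of it (c > 0) and not every usual-care woman calls (q < 1). The size depends on them almost entirely.

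**With the survey alone:** RR = s/s = 1.00 and the false-positive rate is 5%, provided that s really is equal in the two arms.

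**The case against.** The strongest reply is that the article says only that data are gathered from both sources. It does not say that they are pooled, and the Analysis section names no source for the count. A sentence in Outcomes that follows the list of secondary and health outcomes says that these are assessed by patient report, and it can be read to cover utilization too. A condensed article may leave the combining rule to the full protocol or SAP, which are not shown. 211 records are in any case needed to document delivery and crossover. This stands in part. A reader might infer that the between-arm count is defined to include 211 records, and the text does not go that far, so the point is conditional. What remains is a stated choice rather than an omission: 211 reports are named as a source for this outcome, without restriction, and their collection differs by arm.

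A second reply is that the bias may be small. The only scheduled 211 contacts are the first call and the one at 2 weeks, while the surveys run to 18 months. If use is spread over that period, 211 would see little of what the surveys miss. This stands, and it is why the range starts near the null. The opposite is also possible: surveys months apart invite forgetting of early use that 211 asked about at 2 weeks.

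A third reply is that usual-care women who phone 211 are noted. They are, but that capture is passive and limited to callers; the illustration allows for 10% to 20% calling.

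A fourth is that the survey is not a clean instrument either. Women know whether 211 called them, and being asked about services may improve recall in the active arm. Non-response is expected as well, with 20% attrition planned. This stands as a limit on the remedy.

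**Conclusion.** The point holds in conditional form. The article names 211 reports as a source for social service utilization and makes their collection depend on the arm. If those reports enter the between-arm count, ascertainment is unequal and errs in favour of the intervention.

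The size cannot be determined from the article. Under the assumptions shown, the spurious rate ratio runs from about 1.01 with a false-positive rate of about 5% to about 1.3 with about 80%. These figures illustrate a mechanism and do not estimate the bias in this trial.

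A reader might go further and infer that a positive utilization result would be wholly an artefact. The documents do not support that: a patient-reported source covers both arms, usual-care callers are noted, and some plausible inputs give almost no bias. The two primary outcomes, social needs and episode completion, are not touched by this point.

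**What to change.** State in the outcome definition that the between-arm comparison of social service utilization uses the number of services reported in the patient survey, with the same items asked at the same times in both arms. State that 211 records are reported separately, by arm, as data on delivery, engagement and crossover (usual-care women who contacted 211), or at most in a supportive analysis labelled as having arm-dependent ascertainment. If the full protocol or SAP already says this, the article's sentence on data sources needs only to be aligned with it.

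The cost is a change of wording before analysis, using data already planned. Use that 211 recorded but the woman did not report is no longer counted, which loses some sensitivity. The change removes the asymmetry from 211 records only. Arm differences in self-report or in survey non-response remain, so survey response should be shown by arm beside the result.
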